## Introduction

Each year approximately 20 people per 100 000 experience a sudden hearing loss in one ear that is located in the inner ear.^1^ This is called sudden sensorineural hearing loss (SSNHL), defined as a rapid loss of hearing occurring over 3 days, of 30 dB (decibel) or more, over at least three contiguous sound frequencies.^2^ SSNHL is predominantly unilateral and the degree of hearing loss can range from mild to profound. In 71%–90% of cases, the cause is unknown despite investigation, and these cases are termed idiopathic SSNHL.^3 4^

Idiopathic SSNHL is a serious condition, adversely impacting people’s lives^5^ with research showing associations with emotional distress, depression, difficulties at work and impaired social integration.^6 7^ Its prognosis is poorly understood and may depend on age, comorbidities, degree of hearing loss, audiometric configuration, presence of vertigo, treatment received, time between onset of hearing loss and treatment, and other factors. It is estimated that 32%–65% of cases of idiopathic SSNHL recover spontaneously, although clinical experience suggests that this may be an overestimation, with further research required in this area.^2 8 9^

Current care pathways for patients suffering from SSNHL appear to vary considerably in terms of the type of service patients first present to, their subsequent referral, length of time between onset of symptoms, presentation and start of treatment, the treatment plan as well as follow-up. The mainstay of treatment options for idiopathic SSNHL include oral steroids, intratympanic steroid injections or a combination of both.^5^ The National Institute for Health and Care Excellence, in their recent guidelines on hearing loss (NG98), highlighted the paucity of evidence assessing the comparative effectiveness of these treatments and issued a high priority research recommendation to identify the most effective route of administration of steroids as a first-line treatment for idiopathic SSNHL.^10^ The National Institute for Health Research (NIHR) Health Technology Assessment Programme has since released a commissioned call for a trial to address this question.^11^

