### Sample size and recruitment

The minimum sample size for developing a multivariable prognostic model to predict recovery for patients with idiopathic SSNHL was estimated using the method reported by Riley *et al*.^14^ Assuming a prevalence (ie, full recovery of idiopathic SSNHL) of between 32% and 65%,^2 8 9^ a Nagelkerke’s R-squared of 0.5,^14^ a 0.05 margin of error in estimation of intercept, and a shrinkage factor of ≥0.95, with our prespecified number of predictor parameters of 15, resulted in a minimum sample size of 510 patients. Assuming that 70% of patients with SSNHL are idiopathic cases, this gives a total study minimal sample size of 730 patients.^3 4^

Ninety-seven NHS trusts across the UK have been identified as study sites via INTEGRATE, SFO-UK, NIHR CRN Audiology Champions and the NIHR CRN. An audit carried out in preparation of this study at five NHS trusts, over 6 months, revealed an average presentation rate of one patient with idiopathic SSNHL per trust per month. It appears therefore that our recruitment target over the study duration (32 months) is feasible.

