### Primary outcome

The change in auditory function in the affected ear from initial presentation to follow-up (at any one time between 6 and 16 weeks from onset of symptoms). Auditory function will be defined as the PTA of air conduction thresholds between the following specific frequencies: 250 Hz, 500 Hz, 1000 Hz, 2000 Hz, 4000 Hz and 8000 Hz. If multiple pure tone audiograms have been carried out between 6 and 16 weeks, the most recent pure tone audiogram will be used for the calculation of auditory function.

Change in auditory function classified as:

Full recoveryFinal PTA in affected ear within 10 dB (≤10 dB) of PTA of baseline pure tone audiogram.OR should a baseline pure tone audiogram not be available:Final PTA in affected ear within 10 dB of PTA of unaffected ear.OR should both ears be affected with hearing loss:Final PTA in affected ear within 10 dB of a normative reference (ISO7029).

Partial to no recoveryFinal PTA in affected ear ≥10 dB of PTA of baseline pure tone audiogram.OR should a baseline pure tone audiogram not be available:Final PTA in affected ear ≥10 dB of PTA of unaffected ear.OR should both ears be affected with hearing loss:Final PTA in affected ear ≥10 dB of PTA of a normative reference (ISO7029).^13^

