### Statistical analysis

We will develop a prognostic model to predict recovery for patients with idiopathic SSNHL and assess the impact of idiopathic SSNHL on patients’ QoL. A multivariable prognostic model will be developed using the candidate predictors specified above (n=15). Missing outcome data at the end of the study will be imputed using multiple imputation by a chained equations procedure.^15^ Internal validation will be performed to quantify optimism in the predictive performance (calibration and discrimination) of the developed model using bootstrapping techniques. Bootstrapping techniques provide information on the performance of the model in comparable datasets and generate a shrinkage factor to adjust the regression coefficients.^16 17^

The mean change in HHIA, HHIE and HUI3 scores across patients with idiopathic SSNHL will be calculated from initial presentation to follow-up (any one time between 6 and 16 weeks). We will use the non-parametric Wilcoxon and McNemar–Bowker tests with a significance level of 5%. Statistical analysis will be carried out using R V.3.6.2 (R Foundation for Statistical Computing, Vienna, Austria).

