### Study procedures

A summary of study procedures is outlined in figure 1. Box 1 provides a summary of all data to be collected. Adult patients with SSNHL presenting to any of the 97 NHS trusts will be assessed for eligibility. In 20 of 97 NHS trusts, all data identified in box 1 will be collected. In the remaining 77 trusts, all data except for QoL data will be collected. In centres where no QoL data are collected, there will be no deviation from the usual standard of care for any patient, and routinely collected patient data will be anonymised; therefore, consent is not required. For centres where QoL data are collected, patients will be provided with a study information sheet and requested to give written consent to participate in the study.

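### The total of 730 carries no allowance for missing 6–16 week audiograms, although the plan expects missing outcomes; the effect is lost precision, modest at plausible loss rates

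*Protocol article*

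**What the plan says.** In the protocol article, Sample size and recruitment, the model calculation "resulted in a minimum sample size of 510 patients" with idiopathic disease. Its inputs are 15 predictor parameters, "a Nagelkerke’s R-squared of 0.5", shrinkage of at least 0.95, an intercept margin of 0.05 and full recovery in 32% to 65%. The next step is: "Assuming that 70% of patients with SSNHL are idiopathic cases, this gives a total study minimal sample size of 730 patients". No other inflation is stated, and no missing-outcome rate appears in the article.

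Four other places bear on whether each recruit will have an outcome:

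- **Primary outcome.** The change in hearing is measured "from initial presentation to follow-up (at any one time between 6 and 16 weeks from onset of symptoms"), so an audiogram in that window is required.
- **Statistical analysis.** "Missing outcome data at the end of the study will be imputed using multiple imputation by a chained equations procedure".
- **Inclusion and Exclusion criteria.** The 72-hour limit concerns how fast the hearing was lost. Neither section limits the time from onset to presentation.
- **Study procedures.** In the 77 trusts that collect no quality-of-life data, "there will be no deviation from the usual standard of care for any patient".

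The Introduction cites a range for the idiopathic share: "In 71%–90% of cases, the cause is unknown despite investigation".

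**The concern.** The printed chain corrects for one loss, patients who turn out not to be idiopathic. It does not correct for a second loss that the same article foresees, idiopathic patients without an audiogram in the window. A patient first seen after week 16 meets the criteria and counts toward 730, but cannot have an in-window follow-up.

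The shrinkage and intercept criteria depend on how much outcome information the data hold. Imputation keeps a patient in the analysis but restores little of that information here. Box 1 lists audiometry at first presentation and at the 6–16 week follow-up only, so no intermediate audiogram informs the imputation. A patient who misses follow-up also lacks that visit's record of treatments given and cause identified. The imputed outcome would therefore rest largely on the predictors already in the model.

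If 730 recruits were taken as meeting the minimum, the article would claim a precision that the data may not have.

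**Working it through.** **1. Reproduce the total.** Inputs from Sample size and recruitment: 510 and 70%.

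510 / 0.70 = 728.6, so 729, printed as 730. In reverse, 730 × 0.70 = 511. The idiopathic share is the only inflation, and the slack is one patient: 1 − 510/511 = 0.2%.

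**2. Observed outcomes at an assumed loss d.** The article gives no rate, so a range is used, at the planning share of 70%: 511 × (1 − d).

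- d = 10%: 460
- d = 20%: 409
- d = 30%: 358

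**3. Loss that 730 tolerates at other idiopathic shares s.** Formula: 1 − 510/(730 × s).

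- s = 71%: 518 idiopathic patients, 1.6% tolerated
- s = 80%: 584, 12.7%
- s = 90%: 657, 22.4%

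**4. Effect on shrinkage.** The criterion is n = P / [(S − 1) ln(1 − R²cs/S)], with P = 15 and R²cs = 0.5 × its maximum. The maximum is 1 − exp{2[φ ln φ + (1 − φ) ln(1 − φ)]}, where φ is the prevalence of full recovery. Start from the n that gives S = 0.95, reduce it by d and solve again for S:

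- d = 10%: about 0.945
- d = 20%: about 0.939
- d = 30%: about 0.931

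The results are the same at prevalence 0.32, 0.50 and 0.65.

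**5. Effect on the intercept margin.** Formula: 1.96 × √(φ(1 − φ)/n). At φ = 0.5, a margin of 0.05 needs (1.96/0.05)² × 0.25 = 384.2, so 385.

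- 20% loss (n = 409), φ = 0.5: 0.0485, within the margin
- 30% loss (n = 358), φ = 0.5: 0.052, outside the margin
- 30% loss, φ = 0.32 and 0.65: 0.048 and 0.049, within the margin

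At φ = 0.5 the limit is passed once loss exceeds 1 − 385/511, about 25%.

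**6. Check the 510.** The same shrinkage formula with S = 0.95 gives:

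- φ = 0.32: R²cs = 0.357, n = 636
- φ = 0.50: R²cs = 0.375, n = 598
- φ = 0.65: R²cs = 0.363, n = 624

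The optimism criterion (311–331) and the intercept criterion (335–385) are smaller, so shrinkage governs. With 510 fully observed outcomes, shrinkage is 0.939, 0.942 and 0.940 at these prevalences. The stated 510 therefore hides no cushion for missing outcomes.

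**7. Recruitment capacity.** The audit rate of one idiopathic patient per trust per month gives 97 × 32 × 1 = 3,104 presentations.

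**The case against.** A reader might infer that 730 recruits cannot deliver the 510 analysable patients the plan promises, and that the plan contradicts itself. The article does not support that, for three reasons.

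- It states 510 patients. It does not call them analysable or say that each has an observed audiogram, and patients with imputed outcomes remain in the analysis. The division itself is correct.
- There is no slack only at exactly 70%, which lies just below the cited 71%–90%. At 80% or 90% idiopathic, 730 could still yield 510 observed outcomes with about 13% or 22% missing.
- The 730 is labelled minimal, nothing says recruitment stops there, and the audit rate allows far more.

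Further points deserve weight. The usual-care sentence explains why consent is not needed; it does not say that follow-up audiograms will be absent, and Study procedures says follow-up data will be collected at 6–16 weeks. Box 1 records variables outside the model, such as examination, laboratory and vestibular results, so imputation may recover something; how much is a judgement. Nothing shows that presentation after week 16 is common. The article is also condensed, and an allowance could be described in the full protocol.

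These points limit the claim to reduced precision of uncertain, probably modest, size. They do not remove the omission. The article prints the whole step from 510 to 730, and that step leaves no room for loss. Possible slack from a higher idiopathic share is not an attrition allowance, and at 71% it covers only 1.6%.

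**Conclusion.** The point holds as an omitted allowance, not as an arithmetic error or a proof of failure. At the planning share of 70%, any loss above 0.2% leaves fewer than 510 observed outcomes. The cost is precision: shrinkage falls from 0.95 to between about 0.945 and 0.931 for losses of 10% to 30%, and the intercept margin is breached only at the top of that range near 50% prevalence.

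This rests on assumed loss rates, on the 70% share, and on imputed outcomes adding little information. The shrinkage figures are relative to a design that truly achieves 0.95. On the stated inputs 510 does not, even with complete follow-up, and that shortfall matters at least as much as the missing allowance.

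**What to change.** In Sample size and recruitment:

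1. Recheck the required number first. The stated inputs give about 598–636, which at a 70% share means 855 to 909 recruits (598/0.70 and 636/0.70) before any allowance for loss.
2. Define the minimum as idiopathic patients with an observed 6–16 week audiogram.
3. State an assumed proportion with an observed outcome, and restate the total as required number / (0.70 × that proportion).
4. Track recruitment in REDCap against observed outcomes, so that patients first presenting after week 16 do not count toward the minimum.
5. If 730 is kept, say that the 510 includes patients with imputed outcomes, and restate the shrinkage and intercept margin delivered.

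Do not simply replace 730 with 911, which is 510/(0.70 × 0.80). That only restores 510 observed outcomes, which gives shrinkage of about 0.94.

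The cost is a reworded paragraph and a less favourable stated total or precision. REDCap already holds the follow-up audiogram, and the larger totals are well within the 3,104 idiopathic presentations that the audit rate implies.

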### Candidate predictors for prognostic model

Age; gender; social class; presence of vestibular symptoms; precipitating illness; pattern of hearing loss; severity of hearing loss; time between onset of symptoms and treatment; treatment(s) received.

Pattern of hearing loss will be defined as: low frequency loss (250 Hz, 500 Hz and 1000 Hz), mid-frequency loss (500 Hz, 1000 Hz and 2000 Hz), high-frequency loss (2000 Hz, 4000 Hz and 8000 Hz) and all frequencies. Severity of hearing loss (on presentation) will be defined as follows: pure tone average (PTA) across six frequencies (250 Hz, 500 Hz, 1000 Hz, 2000 Hz, 4000 Hz and 8000 Hz), classified as: mild (25–40 dB loss), moderate (41–70 dB loss), severe (71–95 dB loss) and profound (>95 dB loss).

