### Inclusion criteria

Adult patients (man or woman) aged over 16 years of age presenting to NHS ENT and hearing services with a history of sudden hearing loss (within a 72-hour window) that is sensorineural in nature.

There is a decrease in hearing of ≥30 dB affecting at least three consecutive frequencies (between the following specific frequencies: 250 Hz, 500 Hz, 1000 Hz, 2000 Hz, 4000 Hz and 8000 Hz), using a premorbid pure tone audiogram as a baseline reference. Or should a baseline pure tone audiogram not be available, the unaffected ear can be used a baseline reference. Or should both ears be affected by hearing loss, a normative reference (ISO7029)^13^ can be used as the baseline reference.

Willing and able to provide written informed consent.

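### Pattern categories miss some eligible audiograms and overlap for others, and severity has no band below 25 dB, so some eligible patients have no defined value on a candidate predictor

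*Protocol article*

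**What the plan says.** Under *Inclusion criteria*, the protocol article requires: "There is a decrease in hearing of ≥30 dB affecting at least three consecutive frequencies". The frequencies are the six standard ones from 250 to 8000 Hz.

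Under *Candidate predictors for prognostic model*, it lists nine predictors, two of which are pattern and severity of hearing loss. Both are defined there and not left for later:

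- Pattern has four categories: low-frequency (250/500/1000 Hz), then "mid-frequency loss (500 Hz, 1000 Hz and 2000 Hz), high-frequency loss (2000 Hz, 4000 Hz and 8000 Hz) and all frequencies".
- Severity is the six-frequency PTA at presentation, in four bands: "mild (25–40 dB loss), moderate (41–70 dB loss), severe (71–95 dB loss) and profound (>95 dB loss").

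The section gives no rule for a run of frequencies that matches no category or contains two. It has no band below 25 dB, and it does not say whether the decibel figures are absolute level or loss from baseline. *Primary outcome* defines auditory function as the PTA of air-conduction thresholds, which is an absolute level.

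**The concern.** A predictor in a prognostic model needs one defined value for every patient in the target population. Here the entry rule and the predictor definitions use the same six frequencies but do not fit together, so the study can enrol patients whom its own coding cannot place.

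The model is the second study objective and drives the sample size. If the coding of two audiometric predictors has to be settled once the audiograms are in hand, part of the prespecification is lost. Anyone who later applies the model meets the same gaps. Adding categories to close them would also add parameters to the 15 on which the sample size rests.

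A second, smaller cost comes from banding PTA. It treats 41 dB and 70 dB as the same and 40 dB and 41 dB as different, although the study records the underlying number.

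**Working it through.** The plan states no figure for this point, so there is none to reproduce. The check sets the entry rule against the predictor definitions.

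**Pattern.** Inputs: six ordered frequencies and at least three consecutive ones affected (*Inclusion criteria*); four categories (*Candidate predictors*). I assume that a frequency counts as affected by the 30 dB entry threshold, because the predictor section gives no threshold of its own.

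Contiguous runs of length 3, 4, 5 and 6: 4 + 3 + 2 + 1 = 10. Two readings are possible. Under *exact*, the run must equal the category. Under *contains*, the run belongs to any category whose three frequencies it includes, and the all-frequency category needs all six.

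| Run (Hz) | Exact | Contains |
|---|---|---|
| 250–1000 | low | low |
| 500–2000 | mid | mid |
| 1000–4000 | none | none |
| 2000–8000 | high | high |
| 250–2000 | none | low and mid |
| 500–4000 | none | mid |
| 1000–8000 | none | high |
| 250–4000 | none | low and mid |
| 500–8000 | none | mid and high |
| 250–8000 | all | all |

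Exact: 4 of 10 fit and 6 fit none. Contains: 6 fit exactly one, 1 fits none, 3 fit two. If isolated extra frequencies are also allowed beside a qualifying run, there are 20 eligible sets. Exact: 4 fit and 16 do not. Contains: 14 fit one, 2 fit none, 4 fit two. No reading gives every eligible audiogram exactly one category.

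**Severity.** Inputs: 30 dB at three of six frequencies (*Inclusion criteria*); lowest band limit 25 dB (*Candidate predictors*). I assume no change at the remaining frequencies.

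- Mean loss from baseline, three frequencies: 3 × 30 / 6 = 15 dB. Four frequencies: 4 × 30 / 6 = 20 dB. Both lie below 25.
- Average loss needed at three frequencies to reach the lowest band: 25 × 6 / 3 = 50 dB.
- Absolute PTA for the minimal three-frequency loss with a flat baseline *b*: *b* + 15. This gives 15 dB for *b* = 0 and 20 dB for *b* = 5 (no band), and 25 dB for *b* = 10 (mild).

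The gap below 25 dB therefore exists on both readings, and is wider if loss from baseline is meant. The same patient (flat 10 dB baseline, minimal loss) is mild on one reading and unclassified on the other.

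**Band edges.** If thresholds are recorded in 5 dB steps (an assumption; the article does not say), the six-frequency mean moves in steps of 5/6 = 0.83 dB. Values such as 40.83 and 70.83 then fall between the integer limits. Rounding to whole decibels closes these gaps. There is no gap at 95, and no PTA falls in two bands.

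**The case against.** The best defence is that this is a coding detail. Audiometry results are collected for every patient and uploaded to one database, so a single central rule can be applied at analysis, and tie-breaks and rounding are ordinary analysis-plan content. For the band edges at 40–41 and 70–71 that defence succeeds. For the rest it does not: the article states the categories as the definition, and a later plan would have to change them, not merely add detail.

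Several stronger readings are tempting, but the document does not support them.

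- *Both predictors overlap.* Only pattern does, and only on the contains reading. The severity bands are mutually exclusive; their fault is incompleteness.
- *Most eligible patterns are unclassifiable.* The count of 6 in 10 needs exact matching, and runs are not patients. On the more generous reading it is one run with no category and three with two.
- *Every minimally eligible patient falls below the lowest band.* On the absolute-level reading, a flat baseline of 10 dB or more brings the patient to at least 25 dB.
- *Unclassified patients will be dropped, or coded differently from site to site, biasing the model in a known direction.* Nothing in the article says so. *Statistical analysis* mentions imputation of missing outcomes and is silent on predictors that cannot be classified.
- *Continuous coding would make the stated minimum of 510 correct.* The article gives 15 parameters without a breakdown, so the saving is unknown. With the stated inputs (Nagelkerke R-squared 0.5, shrinkage 0.95) at 32% recovery, the shrinkage criterion needs 509 patients for 12 parameters but 552 for 13. The point does not bear on 510 either way.

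**Conclusion.** The concern holds in a limited form. Pattern is not exhaustive and can overlap: at least one qualifying run (1000/2000/4000 Hz) fits no category on either reading, and three others contain two. Severity is not exhaustive: it has no band below 25 dB, although the entry rule admits a mean loss of 15 dB, or an absolute PTA of 15 or 20 dB with a flat baseline of 0 or 5 dB. Its scale is also ambiguous.

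Some eligible patients therefore have no defined value on a candidate predictor. How many is unknown, because the article gives no distribution of audiograms or baseline hearing. The pattern result assumes that the entry threshold decides which frequencies are affected. The severity figures assume no change at the other frequencies and, for absolute PTA, a flat baseline. The loss of information from banding is a separate, secondary reason for change. Eligibility, the outcome and data collection are not affected, but the coding should be settled before the model is fitted.

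**What to change.** 1. Enter presenting six-frequency PTA as a continuous predictor, for example with a restricted cubic spline. State whether it is the absolute air-conduction level, as under *Primary outcome*, or loss from baseline.
2. Derive pattern centrally from the recorded thresholds. Either use continuous frequency contrasts (for example mean loss at 250–1000 Hz minus mean loss at 2000–8000 Hz, with a further contrast if mid-frequency loss is to be told apart from loss at all frequencies), or write one prespecified rule that assigns every eligible audiogram to exactly one category. The rule should say what makes a frequency affected.
3. If severity bands are kept for descriptive tables, make them complete: <25, 25 to 40, >40 to 70, >70 to 95 and >95 dB.
4. Recount the predictor parameters after these changes and set the count against the 15 used for the sample size.

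The cost is specification wording only, since audiometry results are already being collected. The one drawback is a less familiar presentation of severity and pattern, which descriptive bands largely offset.

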### Secondary outcomes

1. Degree of change in auditory function

Complete recoveryFinal PTA in affected ear within 10 dB (≤10 dB) of PTA of baseline pure tone audiogram.OR should a baseline pure tone audiogram not be available:Final PTA in affected ear within 10 dB of PTA of unaffected ear (≤10 dB).OR should both ears be affected with hearing loss:Final PTA in affected ear within 10 dB of a normative reference (ISO7029).^13^Marked recoveryPTA improvement ≥30 dB (and final PTA in affected ear ≥10 dB of PTA of baseline pure tone audiogram).OR should a baseline pure tone audiogram not be available:PTA improvement ≥30 dB (and final PTA in affected ear ≥10 dB of PTA of unaffected ear).OR should both ears be affected with hearing loss:PTA improvement ≥30 dB (and final PTA in affected ear ≥10 dB of a normative reference (ISO7029)).^13^Slight recoveryPTA improvement ≥10 dB and <30 dB (and final PTA in affected ear ≥10 dB of PTA of baseline pure tone audiogram).OR should a baseline pure tone audiogram not be available:PTA improvement ≥10 dB and <30 dB (and final PTA in affected ear ≥10 dB of PTA of unaffected ear).OR should both ears be affected with hearing loss:PTA improvement ≥10 dB and <30 dB (and final PTA in affected ear ≥10 dB of a normative reference (ISO7029)).^13^No improvementPTA improvement <10 dB (and final PTA in affected ear ≥10 dB of PTA of baseline pure tone audiogram).OR should a baseline pure tone audiogram not be available:PTA improvement <10 dB (and final PTA in affected ear ≥10 dB of PTA of unaffected ear).OR should both ears be affected with hearing loss:PTA improvement of <10 dB (and final PTA in affected ear ≥10 dB of a normative reference (ISO7029)).^13^

2. Change in QoL score from initial presentation to follow-up at any one time between 6 and 16 weeks following treatment. QoL will be measured with the Hearing Handicap Inventory for Adults (HHIA) (for patients under 65 years of age) or Hearing Handicap Inventory for Elderly (HHIE) (for patients over 65 years of age) and the Health Utility Index Mark 3 (HUI3). QoL data will be collected from a subset of 20 trusts.

Out-of-limit thresholds obtained on the pure tone audiogram will be classified as a 96 dB loss at that specific frequency.

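### The severity predictor is a four-band presenting PTA, while recovery is judged against each patient's reference PTA; the starting gap and the reference are not candidate predictors

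*Protocol article*

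**What the plan says.** All places are in the Methods and analysis section of the protocol article.

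- **Candidate predictors.** The hearing-related entries close the list: "pattern of hearing loss; severity of hearing loss; time between onset of symptoms and treatment; treatment(s) received". Severity is specified as "Severity of hearing loss (on presentation) will be defined as follows: pure tone average (PTA) across six frequencies", "classified as: mild (25–40 dB loss), moderate (41–70 dB loss), severe (71–95 dB loss) and profound (>95 dB loss"). Pattern is a grouping by frequency range: "Pattern of hearing loss will be defined as: low frequency loss (250 Hz, 500 Hz and 1000 Hz), mid-frequency loss", followed by high-frequency loss and all frequencies.
- **Primary outcome.** "Auditory function will be defined as the PTA of air conduction thresholds between the following specific frequencies", the same six frequencies as for severity. Full recovery means a final PTA within 10 dB of a reference: the baseline audiogram, or the unaffected ear if there is none, or ISO7029 if both ears are affected.
- **Inclusion criteria.** The qualifying drop of at least 30 dB is judged "using a premorbid pure tone audiogram as a baseline reference", with the same two fallbacks.
- **Statistical analysis.** "A multivariable prognostic model will be developed using the candidate predictors specified above (n=15").

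**The concern.** The outcome is a difference from a reference, but the severity predictor is a level with no reference stated. Two patients with the same presenting PTA and different previous hearing face different tasks to count as fully recovered, and the model gives them the same severity value. The quantity that separates them can be calculated from audiograms already used for eligibility and outcome. Age can stand in for previous hearing only in part, and pattern says which frequencies are affected, not by how much.

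Objective 2 is a model that predicts recovery, so the cost would be weaker discrimination than the collected data could support. The bootstrap in the analysis section corrects for optimism. It cannot restore information dropped before the model is fitted. The sample size calculation also assumes a Nagelkerke R-squared of 0.5, which is harder to reach if prognostic information is set aside.

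**Working it through.** **1. What the definitions imply.** Write R for reference PTA, P for presenting PTA, F for final PTA, and G = P − R for the starting gap. Full recovery is F − R ≤ 10. Since F = P − improvement, this is the same as improvement ≥ G − 10. So G is the baseline value of the outcome and sets the amount to be regained.

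**2. What one band mixes.**

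- P = 65, R = 5: G = 60, so at least 50 dB must be regained. P = 65, R = 35: G = 30, so 20 dB. Both patients are moderate.
- G = 35 with R = 5 gives P = 40, which is mild. G = 35 with R = 40 gives P = 75, which is severe.
- The moderate band (41–70 dB) means a gap of 31–60 dB when R = 10 and 11–40 dB when R = 30.

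**3. Patients below the lowest band.** Entry needs a 30 dB drop at three frequencies. With no change at the other three, the six-frequency gap is 3 × 30 / 6 = 15 dB. From a flat 5 dB reference, P = (3 × 35 + 3 × 5) / 6 = 20 dB, below the 25 dB at which the mild band starts.

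**4. Size, by simulation.** The protocol gives no spread of reference PTA, no recovery mechanism and no expected c-statistic, so there is no figure of its own to reproduce here and all inputs below are assumptions. Six-frequency audiograms were simulated for 60,000 patients per scenario. Reference thresholds rose with age and had a between-patient SD of 5, 10 or 15 dB. Thresholds were capped at 96 dB and no patient was excluded for severity. Three mechanisms were tried: a recovered amount unrelated to the gap (additive), a recovered share of the gap (proportional), and a recovered share depending only on presenting PTA (absolute). Full recovery came out at 34% to 48%, inside the protocol's 32%–65%. Every model included pattern and age. c-statistics:

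| Mechanism | SD of R | Planned bands | Continuous PTA instead of bands | Bands + gap |
|---|---|---|---|---|
| Additive | 5 | 0.747 | 0.771 | 0.787 |
| Additive | 10 | 0.736 | 0.748 | 0.784 |
| Additive | 15 | 0.727 | 0.734 | 0.785 |
| Proportional | 5 | 0.611 | 0.619 | 0.627 |
| Proportional | 10 | 0.603 | 0.607 | 0.625 |
| Proportional | 15 | 0.600 | 0.604 | 0.626 |
| Absolute | 5 | 0.794 | 0.843 | 0.838 |
| Absolute | 10 | 0.807 | 0.851 | 0.838 |
| Absolute | 15 | 0.818 | 0.856 | 0.841 |

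Adding the gap raises the c-statistic by 0.016 (0.627 − 0.611) to 0.058 (0.785 − 0.727). Refitting with the change proposed below (continuous gap plus reference PTA in place of the bands) gave gains in that same range. Under the absolute mechanism un-banding alone gains 0.038 to 0.049 and does at least as well as bands plus gap. Under the additive mechanism with SD 10, un-banding gives 0.012 of the 0.048. Nagelkerke R-squared moves from 0.21 to 0.33 (additive, SD 15) and from 0.038 to 0.060 (proportional, SD 15).

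**5. Parameter cost.** Four dummy-coded bands use 3 parameters. A 3-knot spline for the gap (2) plus a linear reference term (1) also uses 3, so 15 stays 15. Adding a linear gap on top of the bands would make 16. By the shrinkage criterion of the cited sample size method, n = p / [(S − 1) ln(1 − R²cs / S)], where p is the number of parameters, S = 0.95 and R²cs is half its maximum. At 32% recovery this gives 636 for 15 parameters and 679 for 16; at 65% it gives 624 and 665. These exceed the protocol's 510, which is a separate matter and does not bear on this point.

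**The case against.** **Is severity really absolute?** The bands are labelled as dB loss, and the inclusion criteria treat loss as a decrease from a reference. A reader might take the out-of-limit rule, "Out-of-limit thresholds obtained on the pure tone audiogram will be classified as a 96 dB loss at that specific frequency", as proof that dB loss means a raw threshold. It supports that reading, because it attaches the word loss to a single threshold just above the profound cut, but it is a scoring rule and does not define the predictor. Absolute remains the natural reading of a PTA on presentation. If loss from reference was meant, only the banding and the unclear wording remain.

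**Is it the only baseline hearing term?** No. Pattern is listed too, and if it records which frequencies dropped by 30 dB it carries some gap information: a drop at all six implies a gap of at least 30 dB, a drop at three can mean about 15 dB. The gains above are over a model that contains pattern and age.

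**Could a larger loss be claimed?** A simulation in which recovery depends on the gap alone, with presenting PTA above 96 dB excluded, leaves the bands with only 40%–61% of the likelihood-ratio information of the continuous gap. The documents support neither condition: they state no mechanism, and the protocol has a profound band above 95 dB. In a comparable set-up with profound patients kept, the bands' share of the information in gap plus reference was 0.55–0.69 (gap-driven), 0.76–0.82 (mixed) and 0.83–0.86 (absolute).

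**Are predictions biased in a known direction?** A reader might infer that patients with poor previous hearing get too low a predicted chance of recovery. That holds only if poor previous hearing shortens the distance without itself worsening prognosis, which no section says.

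**Is this left to the analysis plan?** Spline and knot choices commonly are. The predictor list, the severity definition and its cut-points are fixed in the article, and the analysis section commits the model to that list.

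**Conclusion.** The point stands as a cheap improvement. It is not an internal contradiction and does not invalidate the model. On the natural reading, the only term for baseline hearing level is a banded absolute PTA, and the baseline value of the outcome is available but not a candidate.

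The size cannot be derived from the documents. On the assumed distributions, with profoundly affected patients kept, the gain in c-statistic is roughly 0.02 to 0.06. How it splits between un-banding and the gap depends on the recovery mechanism and on the spread of reference PTA, both unknown here. The direction is firmer than the size: the c-statistic rose in every scenario tried, and because G + R = P, linear terms for gap and reference contain linear presenting PTA as a special case.

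**What to change.** Under Candidate predictors, replace the four-band severity predictor by two continuous terms:

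- the presenting gap, defined as presenting six-frequency PTA in the affected ear minus the six-frequency PTA of the same reference used for the outcome, allowing non-linearity (for example a 3-knot restricted cubic spline);
- the reference PTA.

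Presenting PTA plus reference PTA is an equivalent pair when both are linear. If one term is curved, prespecify which. Keep mild, moderate, severe and profound for descriptive tables, and say how patients below 25 dB are shown. State how the 15 parameters are divided among the listed predictors and recount them; the change uses about three, as dummy-coded bands would. If dB loss was meant as loss from reference, say so and still enter it as continuous.

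The cost is wording in two sections, with no new visits, patients or data. The downside is that a user of the model must enter the reference PTA, which may come from a premorbid audiogram, the other ear or ISO7029. These sources are not interchangeable, so the source should be recorded.
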